#### Phase III: Qualitative study

##### *Study design*

A qualitative description [56] approach will be followed to examine the acceptability of the DSM coaching program. This approach allows the researcher to explore participants’ perspectives and understand the barriers and facilitators of a given phenomenon [56, 57]. Hence, the study will explore the acceptability of the DSM coaching program, including the participants’ perspectives on the program, the challenges, and the enablers of implementing the program in the primary care context.

##### Sampling procedure and sample size

A purposive sampling method with a maximum variation technique [58] will be used to include participants of different genders, duration of diabetes, educational status, and program adherence level. The study will recruit ten individuals with type 2 diabetes who participated in the DSM coaching program.

##### *Recruitment of participants*

At the end of the group DSM coaching session, the principal investigator and the research assistant will invite eligible participants to participate in the in-depth interview.

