**Methods:**

The study will employ a mixed-method feasibility randomized controlled trial design. Forty individuals with type 2 diabetes will be randomly allocated to treatment and control groups using block randomization. The primary feasibility outcomes include acceptability, eligibility, recruitment, and participant retention rates, which will be computed using descriptive analysis. The secondary outcomes are self-efficacy, self-care activity, quality of life, and glycated hemoglobin A1c. For normally distributed continuous variables, the mean difference within and between the groups will be determined by paired sample Student *t*-test and independent sample Student *t*-test, respectively. Non-parametric tests such as the Mann-Whitney *U* test, the Wilcoxon signed rank test, and the Friedman analysis of variance test will determine the median difference for variables that violated the normality assumption. A repeated measure analysis of variance will be considered to estimate the variance between the baseline, post-intervention, and post-follow-up measurements. A sample of 10 volunteers in the treatment group will participate in the qualitative interview to explore their experience with the diabetes self-management coaching program and overall feasibility. The study will follow a qualitative content analysis approach to analyze the qualitative data. Qualitative and quantitative findings will be integrated using a joint display technique.

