#### Sample size determination

A formal sample size calculation will not be applied for a feasibility RCT study [34]. Hertzog [35] suggests that a sample size of 10–40 participants per group is enough for feasibility studies (Hertzog, [35]. Hence, considering the study’s pilot nature, the intervention’s high intensity, and the limited research fund, we will recruit 40 participants. Twenty participants will be allocated to each arm of the study with a 1:1 ratio.

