**Fig 1 Fig1:**
[figure not shown]
Study participant flow diagram based on the CONSORT guideline [29]. Key: *T1*, *T2*, *T3* represent time of assessment, *n* number

*Treatment group:* The treatment group will attend a 12-week DSM coaching program culturally adapted from the I-change model [27], an evidence-based health coaching intervention [20]. The DSM coaching program will have six interactive group sessions, including an overview of diabetes, goal setting, dietary management, exercise, blood glucose monitoring and medication, and foot care. In addition, the DSM coaching will also include four individual home-based coaching sessions. Furthermore, a family member who is a direct care provider will have a 10-min orientation after every individual home-based coaching session with the participants.

The principal investigator, who has completed a coaching and counseling course at Queen’s University, Kingston, Canada, will facilitate the DSM coaching sessions. The coach will deliver six 2-h group coaching sessions every 2 weeks for 3 months. The coach will use interactive discussions, experience sharing, demonstration, and home-take assignments to address the program goals. The intervention group will also continue receiving the usual care in the clinic (see Additional file 1: the DSM coaching program).

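### Interviewees are invited by the coach at the end of the group session, which is in tension with sampling by adherence level and may tilt the acceptability interviews toward approval

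*Protocol article*

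**What the plan says.** All references are to the Protocol article.

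- **Sampling procedure and sample size (Phase III)** specifies purposive, maximum-variation sampling, intended to "include participants of different genders, duration of diabetes, educational status, and program adherence level". The pool is those who took part in coaching: "The study will recruit ten individuals with type 2 diabetes who participated in the DSM coaching program".
- **Recruitment of participants (Phase III)** fixes the occasion and the inviters: "At the end of the group DSM coaching session, the principal investigator and the research assistant will invite eligible participants".
- **Intervention arms of the study, treatment group**, states that the principal investigator "will facilitate the DSM coaching sessions". The programme has six group sessions and four home-based individual sessions.
- **Data collection (Phase III)** gives the interviews themselves to an experienced qualitative researcher.
- **Study participant retention** has the research assistant follow attendance and telephone participants before sessions.
- **Study design (Phase III)** and **Data integration** give the purpose. The interviews explore acceptability, challenges and enablers, and are combined with the quantitative results to answer the feasibility questions.

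**The concern.** Two features of the recruitment sentence work against the sampling plan in the section just before it.

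The first is reach. An invitation issued at a group session reaches whoever is there. A low adherer is, by the article's own definition, someone who misses sessions. The recruitment point is therefore related to one of the axes on which the sample is meant to vary, and Phase III names no route to people who are absent.

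The second is the inviter. One of the two people asking is the coach whose programme is being judged. Someone dissatisfied with the coaching may find it easier to decline than to accept and then criticise.

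Both push the same way: toward attenders and people on good terms with the coach. Acceptability is part of the primary objective. The acceptability scale gives a score and the attendance sheets give counts, but the interviews are the only stated source of participants' own accounts of what kept them away or what they disliked. The definitive trial is to be designed from this evidence, and a gap in who was interviewed cannot be repaired at analysis.

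**Working it through.** The plan states no figure on this point, so there is none to reproduce. The check is a comparison of sections, followed by a short illustration of why the size stays unknown.

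**Sections side by side**

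1. Sampling needs people at different adherence levels. Under Adherence rate, the threshold is 80% of group plus individual sessions. With 6 + 4 = 10 sessions, that is 0.80 × 10 = 8 sessions, so a person below it has missed at least three.
2. Recruitment places the invitation at the end of the group session. It does not say which session, or whether the phrase marks a place (those in the room) or only a time (once the group programme has finished).
3. Read as a place, people absent that day are not invited. Read as a time, they could be, but nothing in Phase III says so.
4. On either reading the coach is one of the two inviters.
5. The separate interviewer acts after invitation and consent. That may ease frank speech in the interview, but it cannot change who was asked or who agreed.

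**Illustration of reach (assumed inputs)**

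- Arm size 20, from Sample size determination: "Twenty participants will be allocated to each arm of the study with a 1:1 ratio".
- Low attenders: 4, assumed. This is the number left if adherence just meets the 80% progression criterion in Table 1: 20 × (1 − 0.80) = 4.
- Probability *p* that a low attender is at the session where invitations are made: not in the document, so varied. Attendance is taken as independent between people.
- Reading taken: only those present are invited.

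Expected number of low attenders present = 4*p*. Chance that none is present = (1 − *p*)^4.

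| *p* | Expected present | Chance none present |
|---|---|---|
| 0.70 | 2.8 | 0.30^4 = 0.8% |
| 0.50 | 2.0 | 0.50^4 = 6% |
| 0.33 | 1.3 | 0.67^4 = 20% |
| 0 (all stopped coming) | 0 | 100% |

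The table counts who can be reached, because purposive selection can pick out any low attender who is present but none who is absent. From the full list, all four could be approached. The direction is the same in every row. The size depends entirely on *p*, which the document does not give. The reluctance of critics to accept the coach's invitation cannot be quantified at all.

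**The case against.** The other side has several good arguments.

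- **The phrase may be a time point.** Adherence to the group sessions is known only once they are over, so inviting then makes sense for a sample chosen partly on adherence. The sentence speaks of eligible participants and does not limit invitations to those present. This stands. A reader might infer that the two sections contradict each other and that the planned sample cannot be filled, but the text supports only a tension and a risk.
- **The sampling is purposive.** A reader might treat the ten interviewees as a random draw from those present and compute the chance of missing every low attender. That is not the procedure described: a low attender who is present would be sought out. This stands, and no such probability is used here.
- **Low adherence need not mean absence from the group.** Someone who attends all six group sessions and one of the four home sessions has 7 of 10, below the threshold, and may well be in the room. This also stands. It narrows the problem to people who miss group sessions or stop altogether.
- **The research assistant also invites**, and already tracks attendance and makes calls. So it does not follow that the coach approaches every interviewee, and the means of contacting absentees exist. However, the calls described are session reminders and are not tied to interview recruitment.
- **The word volunteers.** The abstract says: "A sample of 10 volunteers in the treatment group will participate in the qualitative interview". A reader might take this as self-selection by rapport. The Study setting section uses the same word for people consenting to the trial, so it shows no more than consent.
- **The article is condensed.** Contact procedures and quotas may sit in a fuller protocol. That would answer a complaint about missing detail. Here, however, the article states an inviter and an occasion, and both sit badly with its own sampling aim.

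**Conclusion.** The point holds as a risk of selection at invitation. As written, recruitment through the coach at the end of the group session may miss people who skip or leave the sessions, and may draw fewer of those critical of the programme. The acceptability findings may then look more favourable than the coached group's experience. Giving the interviews to a separate researcher does not correct this.

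The reach part rests on reading the sentence as an invitation to those present, or on nobody pursuing absentees if it is only a time point. The inviter part holds on both readings, but rests on the judgement that critics respond less readily to their own coach. The document does not establish the size of either.

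The randomised comparison and the acceptability scale score are not affected. The change is worth making before recruitment to the interviews, because it bears on a primary objective and costs little.

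**What to change.** Rewrite the Recruitment of participants paragraph in Phase III to say that:

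1. interviewees are selected purposively from the full list of participants randomised to coaching, using the attendance records and including those who stopped attending;
2. the research assistant or the qualitative interviewer makes the invitation, and the coach does not;
3. people absent from sessions are invited by telephone.

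Reserving some of the ten places for people below the adherence threshold would make the adherence axis explicit, but is optional.

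The cost is one paragraph of protocol text and a few extra calls by staff already in the study. The research assistant is already unmasked, so using that role does not affect the blinding of assessors. The downside is that some low attenders will decline, so filling the sample will take slightly longer.

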##### *Data collection*

An experienced qualitative researcher will conduct the interviews. Study participants will sign an informed consent form and have the option to decide on the recording of the interview before the start of the session. A semi-structured interview question addressing the acceptability of the DSM coaching program will be prepared in Amharic to explore the experience of individuals with the DSM coaching program. Interviews will be audio-recorded, transcribed verbatim by a transcriber, and translated into English for analysis.

##### Qualitative data analysis and management

Data will be analyzed using qualitative content analysis [56]. An experienced transcriber will transcribe all the interview records in Amharic. Two of these transcripts will be translated into English by a professional translator and used by the research team to prepare a codebook. The data analysis will follow a three-step inductive content analysis approach: preparation, organization, and reporting of the analysis process [59]. The preparation phase includes selecting the unit of analysis and making sense of the data. The organization phase includes open coding, grouping codes, categorizing, and abstraction. The third step is reporting the findings using a model or conceptual system. NVivo software version 14 will be used to code, categorize, and recategorize the qualitative data [60].

##### *Data integration*

The qualitative and quantitative findings will be integrated at the resulting level [61] and interpreted to answer the feasibility research questions. Data will be presented in a joint display technique to interpret findings (Fig. 2).

**Fig 2 Fig2:**
[figure not shown]
A flow diagram showing the mixed-method data integration process of the DSM coaching program

## Discussion

Self-management strategies rely on individuals’ preferences, build on prior knowledge, recognize contextual factors, and encourage active engagement in chronic illness care [62]. Establishing collaboration between patients, health care providers, family members, and the community at the primary care level is a means for successful self-management of chronic illness [63]. Diabetes self-management in the primary care of Ethiopia is problematic due to poor linkage within the health systems, poor quality of services, and lack of public awareness. Individuals with diabetes may live with the illness for many years and are supposed to manage a significant portion of the self-care activities such as diet, exercise, medication, foot care, and blood glucose monitoring by themselves [63].

In resource-limited settings where community support programs and linkage are lacking, primary care agencies need to think of alternative schemes to address the self-management needs of individuals with diabetes. The practice of self-management strategies like goal setting in the primary care settings is challenged by patient readiness, skill, and attitude, provider’s attitude and skill, and lack of time [64]. Diabetes self-management coaching has shown significant improvement in self-efficacy, self-care behavior, quality of life, and clinical parameters among individuals with type 2 diabetes in developed countries. However, one of the challenges in adapting and tailoring a complex health intervention in resource-limited countries is the program’s acceptability and implementation feasibility. Hence, the current study will explore the acceptability of the DSM coaching program. Furthermore, the study will evaluate the preliminary effectiveness of the DSM coaching program on self-efficacy, self-care activity, quality of life, and HbA1c. Evidence generated from this feasibility/pilot study will be used to design and implement a definitive RCT among individuals with type 2 diabetes.

### Strengths and limitations of the study

The study will introduce a culturally adapted and contextually tailored DSM coaching program through an iterative process supported by a supervisory committee and a panel of multidisciplinary experts. In addition, the study will be the first to introduce coaching as an intervention in the Ethiopian primary care context; hence, it will be a foundation for future definitive trials in the area. Furthermore, the preliminary outcomes of the study will be used to design DSM coaching programs in the context of low-income countries. Due to the nature of the study, the trial implementor, research assistant, and study participants will not be blinded regarding group allocation. The short follow-up period of the study might make it challenging to make a meaningful conclusion on the long-term behavioral outcomes. Furthermore, the lack of adequate information about the amount, type, and effect of processed diets on diabetes management and the effect of religious and cultural practices on diabetes management limits our ability to characterize the study population.

## Data Availability

All required data will be available upon request; please contact the principal investigator.

## Abbreviations

ADA: American Diabetes Association
ANOVA: Analysis of Variance
CIFG: Comprehensive Intervention Fidelity Guide
DSM: Diabetes Self-Management
DSMC-FM: Diabetes Self-Management Coaching Fidelity Measure
HbA1c: Glycated Hemoglobin A1c
IDF: International Diabetes Federation
ITT: Intention to Treat
LMIC: Low- and Middle- Income Countries
WHO: World Health Organization
OPC-FM: Occupational Performance Coaching-Fidelity Measure
RCT: Randomized Controlled Trial
SDSCA: Summary of Diabetes Self-Care Activity
SMRC: Stanford Self-Management Resource Center
SPIRIT: Standard Protocol Item: Recommendations for Interventional Trials
SPSS: Statistical Package for the Social Sciences
TAAS: Treatment Acceptability/Adherence Scale
UGCSH: University of Gondar Comprehensive Specialized Hospital
WHO: World Health Organization
WHO-QoL: World Health Organization-Quality of life
